##### Suicidality

2.4.3.2

Suicidality will be measured in clinical interview (Montgomery–Åsberg Depression Rating Scale (MADRS), Item No. 10 out of 10 items, rated 0-6, with higher values representing more suicidality) and self-report (9-Item Patient Health Questionnaire (PHQ-9) (Item No. 9 out of 9, rated 0–3 with higher scores indicating more suicidality). Completed suicides are recorded as serious incidents.

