
As empirical assumptions for the interplay between depression and loneliness in the inpatient and follow-up depression therapy are rare, we decided to set a change of 2 points in the MADRS per 1 SD of loneliness (3-Item UCLA Loneliness Scale) as the minimum meaningful association that shall be detected via the interaction (baseline x change) over the inpatient and post-treatment course. The model tested baseline loneliness and change in loneliness with at least 1.75 points MADRS as we have no empirical assumptions about which association is more significant for this setting, but we have a theoretical assumption that these single associations are less significant than their interaction. An omnibus likelihood ratio test will evaluate these assumptions in a single model, followed by Holm-Bonferroni corrected single tests to evaluate these three assumptions. This step will also evaluate the direction of effects and theoretical plausibility (more loneliness at baseline and less change in loneliness shall predict higher depressive symptom severity). The primary analysis of the linear mixed model includes all three measurement points as a categorial factor. Potential time- effects will serve as covariates in this model and will be reported exploratory with no influence on sample size calculation. Studies examining the clinical course of inpatient depression treatment measured with the MADRS report partly comparable values of MADRS at baseline (≈ 30 points) (62–64) and discharge, though findings remain heterogeneous (65, 66). Model assumptions for this sample size calculation were therefore based on plausible clinical values: T0 = 30, T1 = 16, T2 = 15 MADRS points, with a constant standard deviation of *SD* = 8 across all time points. Between-person differences in depression symptom severity (MADRS) were considered with fixed and random slopes, and ICC was set at .50. Power simulation involved assumptions of approximately 5% missing completely at random (MCAR) and 10% missing at random dropout at T2 (MAR). Sample size estimation was performed with R using the following packages: lme4, lmerTest, MASS and tidyr. The simulation for the overall model yielded a statistical power of ≥ 80% for all three assumptions at *n* = 172 with 15% combined dropout rate (MCAR, MAR), resulting in a total of *n* = 199. The number of simulations was 500 (nsim = 500) at a significance level of *α* = 0.05 for the omnibus likelihood-ratio test, with Holm-Bonferroni corrected single hypothesis tests. As depression can lead to cognitive distortion, correlations between loneliness and depression might be dependent on the measurement point, and given the insufficient clinical validation of the loneliness measures, it remains unclear whether the assumptions of a normal distribution and the assumed level of measurement adequately describe the interplay between depression and loneliness. Additional statistical methods are employed in an explorative and descriptive manner (generalized linear mixed-effects model and mixed analysis of variance). Power-analysis for mixed ANOVA using G*Power Version 3.1.9.7, with categorical groups of ‘high’ and ‘low’ loneliness (median-split) when considering an α error of 0.05, a power of 0.9 (1-β error probability) and a correlation value among repeated measures of 0.5 for the group’s results an estimated sample size of *n* = 36 participants assuming a medium effect size (*f* = 0.25), and *n* = 214 participants assuming a small effect size (*f* = 0.10).

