###### Montgomery–Åsberg Depression Rating Scale (MADRS)

2.4.1.1.1

Core symptoms of depression will be assessed by using the MADRS (67, 68), which is a widely used semi structured clinician-rated interview consisting of 10 items (*apparent sadness, reported sadness, inner tension, sleep, appetite, concentration, lassitude, inability to feel, pessimistic thoughts, and suicidal thoughts*). Each of these items is rated on a scale from 0 to 6, with a sum score ranging from 0 to 60 points. Higher scores indicate greater severity of depressive symptoms, with scores of 31 or above suggesting the presence of severe depressive syndrome (69). The assessment refers to the preceding seven days and is considered to be suitable for repeated measurements (68, 70).

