###### Depression (self-report): 9-Item Patient Health Questionnaire (PHQ-9)

2.4.1.1.2

The PHQ-9 (71, 72) is a self-report measure that is used to assess depressive symptomatology and is frequently used in both clinical and non-clinical populations (73, 74). It comprises nine items reflecting the DSM-IV criteria for major depressive disorder but remains one of the most frequently used self-report measures. The PHQ-9 is rated on a four-point Likert scale (0 = *not at all*, 1 = *on several days*, 2 = *on more than half of the days*, and 3 = *nearly every day*). The sum score ranges from 0 to 27 and is used to evaluate the severity of depressive symptoms. A score of 20 or higher is indicative of severe depressive syndrome. Moreover, scores ≤ 4 denote no or minimal symptoms, scores between 5 and 9 indicate mild symptoms, scores between 10 and 14 indicate moderate symptoms, and scores between 15 and 19 indicate moderately severe depressive symptoms.

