
Given that the study design does not permit definitive causal conclusions to be determined about the direction of all fixed and random effects, the findings are still expected to provide valuable insights and relevant implications. In particular, the following insights can be obtained (1): a report on whether patients with different levels of loneliness receive equal benefits from inpatient multimodal depression treatment; (2) insights into changes in loneliness during and after depression treatment; (3) important preliminary findings regarding the shared and distinct biopsychosocial mechanisms underlying loneliness and depression; and (4) the relationship of loneliness and depression on to secondary outcomes, including quality of life and suicidality.

Should the primary hypotheses be confirmed — that is, if baseline loneliness, change in loneliness or their interaction is significantly associated with the level of depressive symptom severity across the treatment course — this may carry implications for clinical practice. First, a brief loneliness screening (requiring less than two minutes using the 3-Item UCLA Loneliness Scale) might be considered for integration into routine psychiatric admission assessments, as it may enable clinicians to identify patients at risk for poorer treatment outcomes early in the treatment process — though randomized controlled studies would be needed to determine whether such screening translates into improved clinical outcomes. Second, the exploratory distinction between more situational and more enduring aspects — examined here only descriptively and without a validated state-trait measure — may, if associated with the course of depressive symptom severity, generate hypotheses for future interventional studies. Such studies could evaluate whether loneliness-focused components (e.g., cognitive restructuring of maladaptive social cognitions or facilitated social re-engagement during the transition from inpatient to outpatient care) add value to multimodal depression treatment. Any inference about modifiability would require an interventional design and lies beyond the scope of the present observational study. Third, the finding that loneliness at discharge predicts relapse would underscore the importance of addressing social connectedness as part of discharge planning and aftercare, a dimension that is currently underrepresented in German psychiatric treatment guidelines.

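### Suicidality is scored from items that belong to the MADRS and PHQ-9 totals, so relating it to depression on the same scale at the same visit inflates that link

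*Protocol article*

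**What the plan says.** Section 2.4.3.2 gives two measures of suicidality. The clinician-rated one, scored 0 to 6: "Suicidality will be measured in clinical interview (Montgomery–Åsberg Depression Rating Scale (MADRS), Item No. 10 out of 10 items". The self-report one is from the PHQ-9: "Item No. 9 out of 9, rated 0–3 with higher scores indicating more suicidality".

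Section 2.4.1.1.1 ends its list of the ten MADRS items with "pessimistic thoughts, and suicidal thoughts" and describes the total: "Each of these items is rated on a scale from 0 to 6, with a sum score ranging from 0 to 60 points". Section 2.4.1.1.2 does the same for the PHQ-9: "The sum score ranges from 0 to 27 and is used to evaluate the severity of depressive symptoms".

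The Introduction plans analyses of suicidality as a further clinical outcome. Section 2.6 groups it with the secondary outcomes, to be analysed exploratively and reported descriptively, although its definition stands under Other variables (2.4.3). The Discussion names as an expected insight "the relationship of loneliness and depression on to secondary outcomes, including quality of life and suicidality".

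The article mentions no depression score that leaves the suicidality item out. The M.I.N.I. also characterises suicidality (section 2.2), but Table 1 schedules it at enrollment only, so no separate repeated measure is available.

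**The concern.** Depression severity is the MADRS or PHQ-9 total, and suicidality is one component of each. If suicidality is related to the total of its own scale at the same visit, the outcome stands on both sides of the analysis. Part of the resulting correlation comes from the scoring and says nothing about patients.

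The practical risk is misreading. Suicidality is a clinically important outcome, and the study wants to separate what depression and loneliness each contribute to it. A depression association inflated by scoring would look stronger than it is. If the total were also used as a same-visit covariate, the comparison would tilt against loneliness, the exposure that the study is about.

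**Working it through.** **1. Are the items inside the totals?** MADRS: 10 items × 6 = 60, the stated maximum. PHQ-9: 9 items × 3 = 27, the stated maximum. Without the suicidality item the maxima would be 54 and 24. Both totals therefore include it.

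**2. Inputs.**
- From the article (2.3): MADRS total "with a constant standard deviation of *SD* = 8 across all time points"; analysed n = 172; a cross-sectional loneliness–depression correlation of about 0.50, from non-clinical samples.
- Assumed, not in the article: MADRS item-10 SD 1.0 to 1.6; item-rest correlation 0 to 0.6; PHQ-9 total SD 5 and item SD 0.9 to 1.1; loneliness–rest correlation 0.3 to 0.5; loneliness–item correlation 0.25 to 0.45.

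**3. Depression link.** The rest score is the total minus the suicidality item. Its SD solves SD_total² = SD_rest² + SD_item² + 2 × r(item,rest) × SD_rest × SD_item. Then

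r(item,total) = [r(item,rest) × SD_rest + SD_item] / SD_total.

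- No true link (item-rest r = 0): the result is SD_item / SD_total, from 1.0/8 = 0.125 to 1.6/8 = 0.20. With n = 172 at one visit, the standard error on Fisher's z scale is 1/√169 = 0.077. The artefact alone is then between 0.126/0.077 = 1.6 and 0.203/0.077 = 2.6 standard errors.
- Example, item SD 1.3 and item-rest r = 0.4: SD_rest = 7.39, so r(item,total) = (0.4 × 7.39 + 1.3)/8 = 0.53. The overlap adds 0.13.
- MADRS, item-rest r of 0.4 to 0.6 and all item SDs: the overlap adds 0.08 to 0.16.
- PHQ-9: overlap alone gives 0.18 to 0.22; at item-rest r of 0.4 to 0.6 it adds 0.11 to 0.18.

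A second set of assumptions gives similar sizes. With equal item SDs and an inter-item r of 0.3 among the other items, an unrelated item would correlate 1/√31.6 = 0.18 with the MADRS total and 1/√25.8 = 0.20 with the PHQ-9 total. If the suicidality item also correlates 0.3 with each other MADRS item, it correlates 3.7/√37 = 0.61 with the total and 2.7/√30.6 = 0.49 with the rest.

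**4. Loneliness link, only if the same-visit, same-scale total is a covariate.** With L for loneliness, i for the item and X for the depression score in the model:

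β_L = [r(L,i) − r(L,X) × r(i,X)] / [1 − r(L,X)²].

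Examples for item SD 1.3, item-rest r = 0.4, loneliness–rest r = 0.5:
- r(L,i) = 0.35. Adjusted for the rest score: (0.35 − 0.5 × 0.4)/0.75 = 0.20. For the total, r(L,total) = (0.5 × 7.39 + 0.35 × 1.3)/8 = 0.519, and β_L = (0.35 − 0.519 × 0.532)/(1 − 0.519²) = 0.10.
- r(L,i) = 0.25. Rest score: 0.067. Total: −0.023.

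Across the assumed range:

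| Rest-adjusted β_L | With the total instead |
|---|---|
| 0.20 to 0.36 | 39% to 87% remains |
| about 0.07 | from about 60% down to nothing; the sign can reverse |
| 0 | −0.05 to −0.10 |

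The downward shift is about 0.03 to 0.13. With no depression term in the model, the overlap does not attenuate the loneliness coefficient.

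**The case against.** The strongest reply is that the article never writes down the model at issue. The sentence on suicidality in the Discussion is a list of expected insights, and section 2.6 promises only exploratory, descriptive analysis. Formal specification and the full covariate list are deferred to the supplement, which is not shown. With two instruments, nothing prevents crossing them.

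A reader might infer that the plan adjusts the loneliness–suicidality association for depression severity and so removes it. The documents do not support this. The nearest text, in section 2.6, says that all models control for measures taken at the same timepoint, but its example concerns loneliness and depression and does not mention suicidality. An earlier-visit total as covariate would contain an earlier value of the item, not the outcome itself. Even with same-visit adjustment, a moderate effect is reduced and survives; complete loss arises only for weak effects under assumed inputs.

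That part of the reply stands. It does not dispose of the overlap. The article itself fixes the suicidality measures and both totals, and it states the intention to relate depression to suicidality. The false discovery rate adjustment deals with multiplicity and leaves a scoring artefact untouched. The caveat on discriminant validity in the Discussion concerns loneliness against depression. Crossing instruments avoids a shared item score, but each total still holds its own suicidality item, so overlap in content remains.

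**Conclusion.** The item overlap is certain from the article's own score ranges. Relating suicidality to the same-scale, same-visit total inflates the depression link moderately: r of about 0.13 to 0.20 for the MADRS with no true link, and an addition of about 0.08 to 0.16 at item-rest correlations of 0.4 to 0.6. These sizes rest on an assumed item SD of 1.0 to 1.6 and the article's total SD of 8.

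The effect on loneliness is conditional. It needs adjustment for that same total, which the article leaves unclear, and then amounts to a downward shift of about 0.03 to 0.13 standardised units. The point concerns an exploratory outcome; the primary omnibus test on the MADRS and the sample size are unaffected. It is worth correcting because the bias is predictable and cheap to remove.

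**What to change.** State in sections 2.4.3.2 and 2.6 that whenever suicidality is the outcome, depression severity is scored without the suicidality item: MADRS items 1–9 and PHQ-9 items 1–8. Apply the same rule when instruments are crossed, so that MADRS item 10 is set against PHQ-9 items 1–8 and PHQ-9 item 9 against MADRS items 1–9. Report the loneliness–suicidality association both without and with adjustment for that rest score, and say at which visit the rest score is taken.

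The cost is a scoring rule and a sentence or two in each section. The items are already collected, so no data, visits or participants are added.

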##### Loneliness: 1-Item state vs. trait

2.4.3.3

Given the absence of an established measure capable of differentiating between enduring (trait) and situational (state) loneliness, this aspect is captured by using a newly developed single item: *‘In looking back upon my life, I would say that I have felt …’*. Participants respond to this item on a four-point scale (1 = *mostly lonely throughout my life*, 2 = *lonely from time to time*, 3 = *only lonely at present*, and 4 = *never lonely*). Responses of 1 are intended to represent trait loneliness; options 2 and 3 intend to represent state loneliness; and option 4 indicates no loneliness. The item developed for the study has not been validated. The psychometric properties are being examined on an exploratory basis, even though this study does not meet the methodological requirements for validating a single-item-scale. Accordingly, results from this item will not be used to draw conclusions about whether a patient’s loneliness is of a state or trait nature.

##### Self-reports on personal and lifestyle information

2.4.3.4

Structured assessments are conducted to obtain demographic information and potential covariates associated with treatment outcomes and biomarker levels. The data includes personal characteristics (including sex, age, body weight, height, living situation, employment status, and marital status) and clinical history of depression (including familial occurrence, number of previous episodes, suicide attempts, hospital admissions, and current treatment). Lifestyle variables encompassing substance use (such as smoking, alcohol, cannabis, caffeine, and other drugs), physical activity (including aerobic and resistance training), and dietary habits (including health-conscious diets, yogurt consumption, and recent antibiotic use) are surveyed.

##### Routine clinical data

2.4.3.5

Routine clinical data, including number of therapies participated, treatment setting, medication, and comorbidities, are retrieved from hospital records by the study physicians. Routine clinical data is recorded and classified in a structured manner, for example, medication is structured by substance classes (SRI/SNRI/NaSSA(Mirtazapin)/NDRI (Bupropion)/TZA/MAO-I/SARI (Trazodon)/Agomelatin/other) and treatment strategy (monotherapy/augmented therapy and predefined changes in dosing or substances).

### Data collection

2.5

Eligibility screening and clinical diagnostic screening, along with interviews, are conducted by study physicians, supported by trained study psychologists. Depression is assessed during a clinical interview (MADRS) by the patient’s treatment team, which also determines when the patient will be discharged from the hospital. All of the self-report assessments are collected by the patients themselves using the REDCap (94, 95) online survey application. Biosampling will be exclusively performed among participants recruited at the University Hospital to ensure methodologically consistent and rapid processing. Routine clinical data are primarily extracted from clinical documentation systems and consolidated prior to analysis (similar to other data sources).

### Statistical analysis

2.6

To perform the statistical analysis, IBM SPSS Statistics Version 29 (96) and R (97) are used. To address the primary objective of this study, which is to examine the clinical relevance of the interplay between loneliness and depression in an inpatient and post-inpatient treatment setting, a set of statistical approaches is employed. To address the primary hypothesis, a linear mixed model with likelihood ratio test will be conducted to test against the null hypothesis that baseline loneliness, change in loneliness or their interaction have no additional association with the symptom severity in the course of depression (T0, T1, T2). In the primary linear mixed-effects model, depressive symptom severity (MADRS) is modeled across the three main assessment points (T0 = admission, T1 = discharge, T2 = three-month follow-up), with time entered as a categorical factor. Baseline loneliness at T0 (applied to T0, T1, and T2), the change in loneliness from admission to discharge (applied to T1 and T2), and their interaction (baseline × change) are entered as fixed effects, alongside random intercepts and random slopes capturing individual differences in symptom level and course. Because the length of inpatient stay differs between participants, the individual inpatient treatment duration (days from admission to discharge) is included as a time-related covariate rather than assuming a fixed interval between T0 and T1. The biweekly interim assessments are not part of the primary model and are reserved for the exploratory within-/between-person trajectory analyses described below. The primary test is an omnibus likelihood-ratio test of the null hypothesis that baseline loneliness, change in loneliness, and their interaction jointly show no association with the course of depressive symptom severity; only if this omnibus test is significant are the three individual coefficients examined, with Holm–Bonferroni correction. The formal model specification and the complete list of covariates are provided in the **Supplementary Material** (Section 4 and **Supplementary Table S1**). All models will be controlled for time-effects (e.g., length of inpatient treatment duration), measures obtained at the same timepoint (e.g. explorative analysis of measurement specific associations of loneliness and depression), recruitment site, gender and age and will be tested for further covariates such as social anxiety and social support. The primary analysis sample will include all participants who completed T0 and T1 depression severity measures (MADRS) and loneliness measures (3-Item UCLA). For each questionnaire, missing individual data points are imputed using person-mean imputation, provided that no more than 20% of the data is missing. Participants with an inpatient stay shorter than seven days (post-enrollment exclusion criterion) are not part of the primary analysis set, since no discharge assessment (T1) is obtained for them; where baseline (T0) data are available, they are retained in the sensitivity analyses of all available data. The extent and pattern of missing values will be described for all inference statistical analysis. Given that dropout is likely associated not only with observed characteristics (MAR) but also with unobserved post-discharge symptom severity (MNAR), sensitivity analyses will include pattern-mixture models or selection models to evaluate the robustness of primary findings under MNAR assumptions. As a pragmatic benchmark, a worst-case analysis will be performed assuming that all dropouts at T2 experienced no improvement (last observation carried forward) or deterioration (fixed offset of +5 MADRS points).

Sensitivity analysis will be performed including all available participant data (including T0 only post-enrollment exclusion analysis and analysis of cases with missing data at T0/T1), and further covariates and confounding variables. Additional covariates as medication, comorbidities, social network size and therapy participation, among others, are recorded and classified in a structured manner, for example, medication based on substance classes and treatment strategy (monotherapy/augmented therapy and changes in dosing or substances). Loneliness is being exploratory evaluated in terms of its significance and clinical relevance as a potential predictor of the course and change in severity of depression. For a more differentiated analysis, within-person and between-person variation will additionally be distinguished in an exploratory manner — both for depressive symptom severity and its individual change, and for loneliness and its individual change. The biweekly interim assessments of loneliness and depression are incorporated into this exploratory, hypothesis-generating part of the analysis, which is oriented toward potential intervention targets. It should be noted that, at the interim time points, loneliness is available from the 3-Item UCLA Loneliness Scale, whereas depressive symptom severity is available by self-report only. Accordingly, the PHQ-9 is administered at the biweekly assessments — and likewise at T0, T1, and T2 — to capture self-reported depressive symptom severity.

Secondary outcomes (quality of life, suicidality, social support and others) and biosamples will be analyzed exploratively and reported descriptively. To account for multiple testing in exploratory analysis, p-values will be adjusted using the Benjamini-Hochberg false discovery rate (FDR) procedure. To evaluate prognostic sensitivity and specificity of loneliness measures loneliness at the beginning of inpatient treatment and at discharge, cutoff values for loneliness scores (with 3-Item UCLA and 6-Item DJGLS Loneliness Scales being considered separately) are assessed exploratory by using ROC analysis. The severity of depression symptoms serves as reference standard for predicting response, which is defined as ≥ 50% reduction in MADRS scores from baseline (T0) to discharge (T1), and depression symptom severity measured with MADRS at T2 serves as reference standard for predicting relapse (defined as one or both of the following conditions: ≥ 10 MADRS points more from discharge to follow-up or ≥ 22 MADRS points at follow-up measurement), respectively. The exploratory ROC results are strongly sample-dependent. Because the cutoff values are derived from the present sample, their predictive value and transferability are markedly limited; the ROC analysis should therefore be regarded only as a first attempt at course- and risk-stratification, the validity of which would need to be confirmed in independent samples. A detailed descriptive presentation of all the measurement time points and all variables assessed will be performed, as well as an exploratory analysis using (generalized) linear mixed models.

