###### 3-Item University of California, Los Angeles (UCLA) Loneliness Scale (3-Item UCLA)

2.4.1.2.1

The 3-Item version (49) is a shortened form of the original 20-Item UCLA Loneliness Scale (75–77) and demonstrates comparable main psychometric criteria (50) and thus benefits regarding secondary test criteria (economy, acceptability). Loneliness is measured through three items, including (1) *feeling a lack of companionship*, (2) *feeling left out*, and (3) *feeling isolated from others*, which are rated on a three-point Likert scale (1 = *hardly ever/never*, 2 = *some of the time*, and 3 = *often*). The resulting sum score (range: 3–9) reflects the degree of perceived loneliness, with higher scores denoting greater loneliness. Cutoff values vary across different studies, although thresholds above 4 or 6 points are most frequently used to classify individuals as ‘lonely’.

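### The baseline × change product contains baseline loneliness squared, so real curvature in admission loneliness can be reported as an interaction

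*Protocol article*

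**What the plan says.** Section 2.6 (Statistical analysis) lists the loneliness terms of the primary model: "Baseline loneliness at T0 (applied to T0, T1, and T2"), "the change in loneliness from admission to discharge (applied to T1 and T2"), and the product: "their interaction (baseline × change) are entered as fixed effects". Time is categorical, with random intercepts and slopes. The article names no squared loneliness term. It places the formal specification and the covariate list in a supplement that is not shown.

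The test sequence is an omnibus likelihood-ratio test on the three loneliness terms; "only if this omnibus test is significant are the three individual coefficients examined, with Holm–Bonferroni correction".

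Section 2.3 (Sample size consideration) says the authors "set a change of 2 points in the MADRS per 1 SD of loneliness" as "the minimum meaningful association that shall be detected via the interaction (baseline x change"). Baseline and change are each set at 1.75 points, and power of at least 80% is claimed for all three coefficients at n = 172.

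The section on the 3-Item UCLA scale describes a bounded score: "The resulting sum score (range: 3–9) reflects the degree of perceived loneliness".

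**The concern.** Write L0 and L1 for loneliness at admission and discharge. With change = L1 − L0, the product is L0 × L1 − L0². If change is coded as a reduction, the squared term enters with a plus sign. Centring or standardising does not remove it.

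A change score usually correlates negatively with its own baseline. The product and L0² are then correlated, and a model without L0² passes part of any curvature in L0 to the product.

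What is at stake is attribution. The interaction is one of three confirmatory coefficients and has the largest target effect. If it is significant, it will be read as baseline and change acting jointly. The same result could arise because MADRS bends with admission loneliness alone. The sensitivity analyses named in the article cover missing data, analysis sets, further covariates and the second loneliness scale. None of them addresses functional form.

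**Working it through.** **Inputs from the article.** MADRS means 30/16/15, SD 8, ICC 0.50, about 15% missing in total, effects 1.75/1.75/2, n = 172, omnibus test then Holm at 0.05.

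**Assumed, because the article does not give them.** Standardised predictors; the correlation ρ between baseline and change; the amount of curvature; T2 missingness drawn completely at random.

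**1. The plan's own figure.** Simulating the stated model at n = 172, with ρ from 0 to −0.59 and a random-slope SD of 0 or 3, gives power of 89–93% (baseline), 90–97% (change) and 96–100% (interaction), and 82–90% for all three jointly. The claim of at least 80% reproduces. For the total, 172/0.85 = 202.4 (203) and 172 × 1.15 = 197.8 (198); the stated 199 lies between.

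**2. Baseline–change correlation.** If L0 and L1 have equal SDs and correlate r, then ρ = −√((1 − r)/2). For r = 0.7, 0.5 and 0.3, ρ = −0.39, −0.50 and −0.59.

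**3. Share of curvature absorbed.** For standardised bivariate normal baseline B and change C:
- Cov(B², BC) = 3ρ − ρ = 2ρ
- Var(BC) = 1 + ρ²
- share of post-baseline curvature passed to the product = 2ρ/(1 + ρ²)

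This gives −0.78/1.152 = −0.68, −1/1.25 = −0.80 and −1.18/1.348 = −0.88. At ρ = 0 the share is zero. With scores rounded and clipped to 3–9 it is −0.56 to −0.69.

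**4. False interactions.** True interaction 0, ρ about −0.5, nominal 5% test:

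| Assumed curvature | Acts at | Normal scores | Scores rounded to 3–9 |
|---|---|---|---|
| 1 point/SD² | T0, T1, T2 | 17–18% | 10–13% |
| 1 point/SD² | T1, T2 only | 51% | 29% |
| 0.5 point/SD² | T0, T1, T2 | 5–9% (both score types) | |
| 0.5 point/SD² | T1, T2 only | 11–17% (both score types) | |

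At 1 point the spurious coefficient is about 0.3–0.4 MADRS points when curvature is equal at all visits, and 0.64–0.80 when it is post-baseline only. The all-visit figure is smaller because the product is zero at T0, so the admission data limit the leak.

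The planned omnibus-plus-Holm sequence gives little extra protection, because the two main effects usually pass and leave the interaction at the full 5% level. Over ρ = −0.39 to −0.59 with normal scores and 1 point of curvature, the interaction is declared in 9–18% (all visits) or 35–52% (post-baseline).

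**5. Ceiling only.** Latent loneliness was related linearly to MADRS with no interaction, and observed scores were clipped at 9. With 13–44% of patients at the ceiling, rejection stays at 4–6%.

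**6. Adding baseline squared.** One squared term common to all visits deals with constant curvature, but still leaves 17–32% rejection when 1 point of curvature is post-baseline only. Adding a second squared term at T1/T2 brings rejection to 3–5%.

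**The case against.** Several counter-arguments carry weight.

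- **Amount of curvature.** The article gives none. One point per SD² is more than half of the 1.75-point linear effect (1/1.75 = 57%). At 0.5 points equal at all visits the inflation is slight, and another set of rounded-score runs gave only 8.5–8.6% at 1 point. The spurious coefficient stays well below the 2-point target. This stands: the figures are conditional, and the larger ones need curvature confined to the post-baseline course.
- **Ceiling.** A reader might infer that patients piling up at a UCLA score of 9 would be enough to create a false interaction. Step 5 shows that it is not; the MADRS relation itself has to bend.
- **Primary test.** A reader might also infer that the primary conclusion is compromised. It is not. If MADRS depends on admission loneliness through a curve, rejecting the joint null of no association is still correct. The Discussion treats the hypothesis as confirmed by any of the three terms.
- **Sizing.** Nor is the study sized on the interaction alone. Power is claimed for all three coefficients, and in the reproduction the main effects are the limiting ones.
- **Unseen supplement.** The formal specification could contain a quadratic term. But section 2.6 spells out the loneliness terms and where each applies, without one. Section 2.3 doubts normality and level of measurement, and answers with exploratory generalised mixed models and a median-split ANOVA. Neither separates curvature from interaction.

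**Conclusion.** The point holds as a limited one about interpretation. As specified, the interaction coefficient cannot be told apart from curvature in admission loneliness when change correlates negatively with baseline. With 1 MADRS point/SD² of curvature, a correlation near −0.5 and no true interaction, the nominal 5% test rejects in about 10–18% (curvature equal at all visits) or 29–51% (post-baseline only). At 0.5 points it is 5–9% or 11–17%. These figures rest on the assumed curvature, the assumed correlation and random T2 missingness. The direction of a false interaction depends on how change is coded. The model terms are stated clearly and contain no error of fact; what is missing is protection for the reading of one confirmatory coefficient, and that protection is cheap.

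**What to change.** Leave the primary model and the 3-df omnibus test as they are. Pre-specify one sensitivity run of the primary model that adds centred baseline loneliness squared twice: once at all visits, and once as a separate term at T1/T2. Keep both terms outside the omnibus set. State how change is coded, and interpret the product as a joint role of baseline and change only if it persists in that run.

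No new data are needed. The cost is two degrees of freedom and, at a correlation near −0.5, about 4–5 points of power for a true 2-point interaction in that run (from 99–100% to 94–96%). At a correlation of −0.59 the cost is larger: 91%, against 97–100% without the extra terms.
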